# SYNOPSIS

| **Title of study:**  “The effects of vitamin D supplementation on glucose metabolism and markers of metabolic syndrome in women with Vitamin D deficiency and previous Gestation Diabetes Mellitus” |
| --- |
| **Sponsor:** |
| **Clinical Phase:** |
| **Investigators:**  Investigators will be endocrinologists practicing in Penang General Hospital |
| **Study period:** 1 years  Planned date of first subject enrolment: 1^st^ June 2011……………..  Planned date of last subject completed: 30^th^ November 2011………………. |
| **Objectives:**   - Primary objective:   - To establish efficacy of Vitamin D supplementation compared to Placebo with respect to Glucose Metabolism in female subjects with Vitamin D deficiency and previous Gestational Diabetes - Secondary objectives :   - To establish effect of Vitamin D supplementation with effect to markers of metabolic syndrome namely- BMI, WHR and BP   - To ascertain if 4000iu of Vitamin D3 replacement is adequate in raising plasma 25 (OH) Vit D level to > 80 nmol/L |
| **Methodology:**  This is a randomised, double blind, placebo controlled, parallel group design |
| **Number of patients:**  It is planned to randomise an estimated total of 26 adult patients into this study, with 13 patients randomised into each treatment group. |
| **Number of centres:**  1 |
| **Inclusion criteria:**   - Women with Gestational Diabetes (GDM) on the most recent pregnancy– between 6 and 48 months post partum at time of recruitment to study - Previous GDM defined as-   - Fasting plasma glucose ≥ 7.0 mmol/l or 2-h plasma glucose ≥ 7.8 mmol/l on 75g OGTT performed during gestation OR   - As determined by treating physician during index pregnancy - With no plan to conceive again within the 6 months of study duration - With 75g OGTT at study baseline confirming either Normal respond, Impaired Fasting Glucose (IFG) or Impaired Glucose Tolerance (IGT) - Vitamin D deficiency at baseline – defined as Plasma 25-(OH) D concentration of between 15 and 50nmol/L |
| **Exclusion criteria:**   - Pregnancy - Breast-feeding (defined as women who are providing full breast feeding) - Known Type 1 or Type 2 Diabetes - Newly diagnosed diabetes as shown by study baseline 75g OGTT (WHO definition) - Use of any oral hypoglycaemic agent or Insulin - Concomitant use of antituberculosis medications, antiepileptic medication, vitamin D or calcium supplement. - Intolerant or allergy to Vitamin D supplementation - Women with renal disease or serious co-morbid illness - Severe vitamin deficiency at baseline- as defined as plasma 25(OH) D concentration of < 15 nmol/L |
| **Test treatment, dose and mode of administration:**  Treatment: Vitamin D 3 capsule  Dose: 4000iu  Route: oral once a day |
| **Duration of treatment with study medication:**  6 months |
| **Criteria for evaluation:**   1. Efficacy parameter(s)  - Primary criterion   - Change in glucose metabolism as assessed by area under curve for glucose (AUCgluc) and insulin (AUC ins) post 75 g OGTT   - Change in Insulin sensitivity index as calculated by HOMA –IR^28^ - Secondary criteria   - Change in Insulin Sensitivity index as calculated by QUIKI^27^   - Change in dynamic Insulin Sensitivity using OGTT Insulin Sensitivity (OGIS)^25,26^   - Change in Beta cell function as evaluated by ratio of AUCins to AUCgluc^29^   - Change in Blood pressure (BP), lipid profile, HsCRP, Urinary microalbumin-creatinine ratio, Body Mass Index (BMI) and Waist Hip Ratio (WHR)   - Change in plasma 25-OH- Vitamin D level pre and post replacement |
| **Statistical methods:**   1. Sample size and power considerations   By using nQuery Advisor version 6.01, from paper written by Von Hurst et al (Vitamin D supplementation reduces insulin resistance in South Asian women living in New Zealand who are insulin resistant and vitamin D deficient - a randomised, placebo-controlled trial )^31^, a sample size of 9 will have 95% power to detect a difference in means of 0.700 (e.g. the differences between Group 1 mean, µ1, of 0.800 and a Group 2 mean, µ2, of 0.100), assuming that the common standard deviation is 0.384, with a 0.050 two-sided significance level. By adding 40% dropped out patient in case of lost to follow up or unplanned pregnnacy, the total sample for 2 arms (placebo and treatment group) treatments is 26 patients (13 patients for each arms).  Green et al (Vitamin D status and its association with parathyroid hormone concentrations in women of child-bearing age living in Jakarta and Kuala Lumpur)^15^ found 60% of population to have 25 (OH) Vit D of < 50nmol/L. Assuming a similar prevalence exist in our population, we thus expect to screen at least 44 women to recruit 26 subjects for the study.  Green et al (Vitamin D status and its association with parathyroid hormone concentrations in women of child-bearing age living in Jakarta and Kuala Lumpur)^15^ found 60% of population to have 25 (OH) Vit D of < 50nmol/L. Assuming a similar prevalence exist in our population, we thus expect to screen at least 44 women to retain 26 subjects for the study. |

# LIST OF ABBREVIATIONS

AE Adverse event

BP Blood pressure

BMI Body Mass Index

CRC-Pg Clinical Research Centre, Penang Hospital

CRC-PMC Clinical Research Centre, Penang Medical College

CV Curriculum vitae

GDM Gestational Diabetes Mellitus

GCP Good clinical practice

HOMA-IR homeostasis model assessment-estimated insulin resistance

IEC Independent Ethics Committee

IFG Impaired Fasting Glucose

IGT Impaired Glucose Tolerance

ID Identification

IRB Independent Review Board

OGTT Oral Glucose Tolerance Test

OGIS Oral Glucose Insulin Sensitivity

QUIKI Quantitative insulin sensitivity check index

T2DM Type 2 Diabetes Mellitus

WHR Waist Hip Ratio

mmHg Millimetre mercury

SAE Serious adverse event

#

# INTRODUCTION AND BACKGROUND

**Introduction:**

Gestational diabetes Mellitus (GDM) is a transient state of carbohydrate intolerance occurring during pregnancy with full resolution post-partum. Diagnositc criteria is yet to be uniform but Malaysia has subscribed to the WHO criteria which is fasting plasma glucose of ≥ 7.0 mmol/L and/or 2 hour plasma glucose of ≥ 7.8 mmol/L following 75g OGTT.

GDM is related to both resistance to peripheral action of insulin and impairment of beta cell function made more prominent with hormonal change during pregnancy. Its presence alerts to heightened risk of development of Diabetes in future. 10-50% of women with GDM develop Diabetes Mellitus later on in life ^1^. Data from Malaysia suggest conversion rate as high as 7-9.9% per year^2^. Identification of effective prevention measure in this high risk group is of significant public health concern.

Insufficient level of Vitamin D is increasingly recognized to impact on a plethora of health condition ranging from bone health, to cancer, autoimmune disease, cardiovascular disease and diabetes. Vitamin D deficiency has been shown to cause insulin resistance and impaired pancreatic function.^3,4,5^ Vitamin D deficiency has also been shown to be a risk factor for future development of diabetes^6.7.8,9^ and data from cohort study demonstrate that higher intake of calcium and vitamin D is associated with reduced risk of development of T2DM^10^.

Vitamin D deficiency is more prevalent in women with gestational diabetes with low level correlating with insulin resistance^11,12,13^. Data from Australia suggest that 48% of women with gestational diabetes has vitamin D deficiency as defined by plasma 25 (OH) D level of < 50nmol/L^11^.

There is as yet no data on vitamin D status among women with GDM in Malaysia but there are reasons to suspect deficiency is prevalent. Study suggests that 60% of Malaysian women of child bearing age has vitamin D deficiency^15^. Inadequate intake from diet low in vitamin D, practice of deliberate sun avoidance and fetal utilization through previous pregnancy and lactation are all possible contributing factors. Darker skin pigmentation may be associated with decrease vitamin D conversion^14^.

There are circumstantial evidences to suggest Vitamin D replacement may be an effective preventive measure in this high risk group. Von Hurst et al showed that supplementation with 4000 iu Vit D3/day in population of south asian women with proven vitamin D deficiency was safe and improves insulin resistance^31^ . Other studies have yielded mix results—partly due to variable dose of supplementation and duration of follow up^16,17,18,19,20,21,22^. Some of the studies are of very short duration of less than 7 days^19,20,21^. Previous studies suggest a possible optimal window for vitamin D replacement to effectively influence glucose metabolism. Vitamin D supplementation was shown to have positive effect on glucose metabolism when introduced during early stage of glucose intolerance but no effect when used in patients with established chronic diabetes^21^. On the other spectrum, vitamin D supplementation was shown to improve glucose metabolism in subjects with impaired fasting glucose but not in normal volunteers^17.^  Lack of adequate dosing may have also accounted for failure of many previous studies to demonstrate beneficial effect of Vitamin D replacement. Scragg et al suggest that vitamin D supplementation need to raise blood 25(OH)D levels above 80 nmol/l because diabetes risk is lowest at this levelVitamin D^23^. .

.

Very little is known about vitamin D status of young GDM population in Malaysia. There has been as yet no study evaluating the role of vitamin D supplementation in reducing the future development of diabetes in this high-risk group of past GDM.

We have therefore design a study consisting of 2 phases. The first phase is to evaluate the prevalence of vitamin D deficiency in women with past GDM. The second phase involves recruitment of selected women into the vitamin D intervention trial.

**Hypotheses**

- There is a high prevalence of hypovitaminosis D in past GDM population
- Supplementation of Vitamin D in women with previous GDM and vitamin D deficiency will result in an improvement in glucose metabolism

**Rationale for study design**:

Overall rationale: Considering the high conversion rate from GDM to Type 2 diabetes, it is crucial to identify effective measure of diabetes prevention in this population. Vitamin D deficiency may be potentially an important contributing factor. The study will identify vitamin D deficiency in a group of women with previous GDM to examine if replacement can improve parameters of glucose metabolism. If we can demonstrate the protective effect of vitamin D replacement, it can be used as a simple and cheap solution to prevent future IGT or DM in this at risk group.

Rationale for inclusion exclusion criteria:

- Women who are 6 to 24 months post partum are chosen as immediate postpartum period may be associated with fluctuation in weight and therefore glucose metabolism. A high percentage of women may have already developed diabetes if identified too many years after GDM pregnancy.
- We exclude pregnant women. Vitamin D at dose of 4000iu/ day is safe in for maintainence or prevention of Vit D deficiency is safe and recommended in pregnancy ^24^. However, as the study involves use of placebo, subjects who are found to be pregnant during screening will be excluded from further participation of trial.
- We exclude women who are breastfeeding as they may require a higher dose of vitamin D to achieve adequate plasma vitamin D level, participation in blinded study involving use of placebo cannot be justified.
- There is no current consensus on optimal level of plasma 25(OH) D, though level below 50nmol/L is generally considered deficient by most authorities and linked to metabolic disturbance. There is no current consensus to the level of vitamin D deficiency below which is deemed unsafe. Many women with vitamin D deficiency is asymptomatic and never screened. As the study involves use of placebo, we have chosen arbitrarily to exclude women with plasma 25(OH)D level less than 15nmol/L. Women with symptomatic hypocalcaemia will be excluded and referred for treatment rather than recruited to receive potential placebo.
- Women with chronic renal or liver failure are excluded due to potential impairment in vitamin D activation and utilization.

Rationale for chosen treament regimen:

- The intervention consist of 25(OH)D3 supplement 4000 iu per day , or placebo, in the form of 2 oral capsules , for 6 months. Oral vitamin D is cheap and easy to take. Vitamin D3 is chosen over D2 as it is 3 times more potent and only a third of dose is required. Inadequate dosing is one of the reasons previous interventional studies has shown mixed result. Vitamin D dose given in prevention trials needs to be high enough to raise blood 25(OH)D levels above 80 nmol/l because diabetes risk is lowest at this level of Vitamin D^23^. Supplementation with 4000 iu Vit D3/day in population with proven vitamin D deficiency was safe and effective in raising the plasma 25(OH) D to desired level^31,32,33^.

Rationale for duration of study end point evaluation:

- An end point data of diabetes development will be more clinically relevant but will require a long study follow up duration and with it many other confounding factors of weight change, diet and exercise. We have therefore opted for a 6 months study where the confounding factors can be identified and accounted for.
- 75g OGTT with Glucose and Insulin measurement, with validated calculation of QUICKI, HOMA-IR and OGIS will be used as surrogate markers of impact of carbohydrate tolerance, Insulin resistance and Insulin secretion.

Potential Risks

- We will be using vitamin D3 replacement dose of 4000 iu/day and do not expect any side effects from this dose. Dose of 4000iu/day has been used without side effects in previous studies^31-33^.
- Synthesis of 1,25(OH)_2_D (the most active metabolite of vitamin D) is tightly regulated, vitamin D toxicity usually occurs only if excessive doses (prescription or megavitamin) are taken. Vitamin D 40,000 IU/day produces toxicity within 1 to 4 month in infants. In adults, taking 60,000 IU/day for several months can produce toxicity. In event of toxicity, marked hypercalcemia commonly causes symptoms. Treatment consists of stopping vitamin D, restricting dietary Ca, restoring intravascular volume deficits, and, if toxicity is severe, giving corticosteroids or bisphosphonates.

Reference: Martindale: The Complete Drug Reference

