# TREATMENT AND STUDY PROCEDURES

## Description of study drug/intervention and comparator

Vitamin D3 capsule in the form of Blackmore’s Vitamin D3 1000iu soft gel capsule will be used. Each softgel capsule will contain 1000iu of Vitamin D3. Patient enrolled in study will take daily- 4 softgel capsules of vitamin D3 or matching placebo.

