## Assessment of compliance

Accountability and subject compliance will be assessed by maintaining adequate "drug dispensing" and return forms. Subjects will be required to return all unused study medication, and the pill count will be entered into the CRF.

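### The protocol gives two capsule counts for the same 4000 IU daily dose (2 and 4), and once names the product 25(OH)D3 instead of vitamin D3

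*Protocol*

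**What the plan says.** Two sections of the protocol describe the product in physical terms.

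- **Rationale for study design, under the chosen treatment regimen:** "The intervention consist of 25(OH)D3 supplement 4000 iu per day , or placebo, in the form of 2 oral capsules". The same bullet then says "Vitamin D3 is chosen over D2 as it is 3 times more potent", and the risks paragraph that follows says "We will be using vitamin D3 replacement dose of 4000 iu/day". No capsule strength is given here.
- **Description of study drug/intervention and comparator:** "Each softgel capsule will contain 1000iu of Vitamin D3", and "Patient enrolled in study will take daily- 4 softgel capsules of vitamin D3 or matching placebo". No daily total is given here.

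The Synopsis, the randomisation visit descriptions and the schematic diagram give vitamin D3 at 4000 IU a day, with neither a capsule count nor a strength.

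On compliance, the Assessment of compliance section says "Subjects will be required to return all unused study medication, and the pill count will be entered into the CRF". The Dispensing section provides for 8 weeks of medication at a time. Section 10.3.1 leaves out of the analysis women who did not get their treatment as planned. It does not mention the pill count.

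**The concern.** Substance, unit strength and units per day together define what each woman takes, and each should have one value throughout a protocol. Here the number of capsules per day has two values, for active and placebo alike. The substance has two names, one of which is the plasma analyte that the protocol measures for eligibility and again at study end.

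Three things draw on these details. The first is what is written on labels and in patient instructions. The second is how many capsules make up an 8-week supply. The third is the denominator of any compliance percentage calculated from returned capsules. The dose is also part of what is being studied: the Synopsis asks whether 4000 IU is enough to raise plasma 25(OH)D above 80 nmol/L, and the rationale attributes earlier mixed results partly to inadequate dosing.

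**Working it through.** **Inputs**

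- Stated daily total: 4000 IU (Synopsis, treatment rationale, randomisation visit, schematic diagram).
- Capsules per day: 2 (treatment rationale) or 4 (description of study drug).
- Capsule strength: 1000 IU (description of study drug; no other strength is stated).
- Supply period: 8 weeks = 56 days (Dispensing). Treatment to the final visit: 24 weeks = 168 days (visit table).

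**Daily dose = capsules per day x strength**

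- Four a day: 4 x 1000 = 4000 IU. This reproduces the stated total.
- Two a day: 2 x 1000 = 2000 IU, which is 2000/4000 = 50% of the stated total.
- Strength at which two capsules would supply the total: 4000/2 = 2000 IU each. The protocol states no such strength.

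**Expected capsules taken = capsules per day x days**

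| Period | 2 a day | 4 a day |
|---|---|---|
| 8 weeks (56 days) | 112 | 224 |
| 24 weeks (168 days) | 336 | 672 |

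The visit window of one week either side does not bridge the gap. Over 7 to 9 weeks (49 to 63 days) the counts run from 98 to 126 at two a day and from 196 to 252 at four, so the ranges do not overlap.

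**Compliance if the wrong denominator were used**

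- Takes two a day, scored against four: 2/4 = 50%.
- Takes four a day, scored against two: 4/2 = 200%.

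These percentages are illustrations only, because the protocol writes no expected count.

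**Substance.** The opening sentence of the rationale bullet says 25(OH)D3. Later in that bullet, in the risks paragraph, in the Synopsis, at randomisation and in the description of study drug, the product is vitamin D3. The 25(OH)D3 name for the product therefore stands alone.

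**The case against.** The strongest reply is that this is a slip in a background section. The description of study drug sits under the treatment and procedures heading, names the product, strength and daily number, and agrees with itself and with the stated total. A site working from it would not be misled. Most of this stands, and it limits the point in four ways.

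- A reader might infer that the protocol states two different doses. It does not. Both the rationale and the other regimen statements give 4000 IU, and 2000 IU appears nowhere as the study dose. It arises only by applying one section's strength to the other section's count.
- A reader might infer that two different substances are in contention. One phrase, contradicted within its own bullet, does not support that.
- A reader might infer that correctly treated women would be dropped from the analysis. Section 10.3.1 names no pill-count rule, and the compliance sections give no cut-off. The section on adverse events removes women whose intolerance leads to poor compliance, but it too sets no threshold. Any such rule may sit in an analysis plan that is not at hand.
- The Synopsis might be thought to be part of the conflict. It gives no count or strength and contradicts neither section.

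What the reply does not remove is the contradiction in capsules per day. Only two sections state that figure, they differ twofold, and the protocol does not say which one governs.

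**Conclusion.** The point holds as an internal inconsistency to correct. It is not a flaw in the choice of design. The protocol gives 2 and 4 capsules a day for the same stated 4000 IU. At the only stated strength, the lower count supplies 2000 IU. The expected count per 8-week supply is 112 or 224, a factor of two. The single use of 25(OH)D3 for the product is probably a wording slip and should be corrected at the same time.

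The size rests on two assumptions: that the 1000 IU strength applies to every capsule supplied, and that a supply period is 56 days. The effect on measured compliance is a possible consequence only; it would arise if the pill-count denominator were built from one section and the patient instruction from the other. The documents do not show that this happens. That one description multiplies to the stated total does not settle which is right, and no view is taken here.

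**What to change.** Reconcile the treatment-regimen rationale with the description of study drug. State the substance, the capsule strength and the capsules per day once, so that strength times number equals the stated daily total, and have the rationale refer to that statement. Then check labels, patient instructions, the 8-week dispensing quantity and the pill-count denominator in the case report form against the reconciled text. The sponsor and the investigator must decide which description is correct.

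The cost is a wording correction and a document check. Sample size, randomisation, endpoints and analysis are unaffected.

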## Potential Benefits

Vitamin D deficiency is not routinely tested for due to its high cost. Our study can identify women with vitamin D deficiency and offer supplementation. Vitamin D replacement is of benefit as deficiency causes adverse effect on bone health. Studies have also suggested its role on many chronic illnesses for example common cancers, autoimmune diseases, infectious diseases and cardiovascular health^24^.

Patient are offered OGTT as part of the study, this may identify early clinically silent glucose intolerance or diabetes. Patients who are found to have already developed diabetes will be excluded from the phase 2 vitamin D intervention studies and referred for appropriate management.

# OBJECTIVES

## Primary objective:

To establish efficacy of Vitamin D supplementation compared to Placebo with respect to glucose metabolism in female subjects with Vitamin D deficiency and previous Gestational Diabetes

## Secondary objective(s):

To establish effect of Vitamin D supplementation on markers of metabolic syndrome namely BMI, WHR and BP

## Ancillary objective(s):

To establish effect of Vitamin D supplementation at 4000iu per day on raising plasma 25(OH) vit D level

# STUDY DESIGN

## Overall study design

The study consists of 2 phases: the first phase includes initial recruitment and screening. The second phase includes recruitment of selected individuals into the vitamin intervention trial.

The intervention trial is a prospective, randomized, double-blind, placebo controlled, parallel group trial to assess the efficacy of Vitamin D supplementation on blood glucose and markers of metabolic syndrome in women with Vitamin D insufficiency and previous Gestation Diabetes Mellitus. Study recruitment will cease when the pre determined number of subjects have been enrolled. Recruitment period for study is estimated to be 6 months

At least 44 subjects will be screened in order to recruit 26 subjects for the study.

**Visit 1: Screening:** Otherwise healthy women with previous GDM now 6 to 24 months post partum, who are not breastfeeding and has no plan to conceive again will be invited to participate in the trial.

All women will have screening assessment, which includes:

- Obtain consent
- Medical history – assessment of inclusion/ exclusion criteria
- Record of concomitant medications- intake of vitamin D will be prohibited within 3 months of screening
- Clinical examination- including
  - Blood pressure measurement- average of 3 readings (sitting)
  - BMI
  - Waist: Hip ratio
- Blood investigations: UE/creatinine, LFT, Calcium, lipid profile, HsCRP, Urinary microalbumin-creatinine ratio,—women with chronic renal or liver disease will be excluded
- 75g Oral Glucose tolerance test—with measurement for
  - Glucose and in at time 0,60,90 and 120 minutes—subject with OGTT showing fasting glucose > 7mmol/L and/or 2 hour glucose >11.1 mmol/L will be excluded from study
  - Insulin at time 0, 60, 90 and 120 minutes – only subjects with glucose and vitamin D level fulfilling inclusion criteria will have insulin sample send for measurement
- Blood tests for plasma 25(OH) D-
  - Subjects with level > 50nmol/L will be reassured and excluded from study
  - Subjects with level < 15nmol/L will be diagnosed with Vitamin D deficiency and excluded from study

